### Statistical Considerations

| ***Sample Size Justification:*** Our analysis will be based on a longitudinal regression analysis in which we do not have an estimate of the within-participant correlations. In the worst case, the two follow-up measures provide no more information than a single follow-up, and the power calculation is equivalent to that for a simple t-test. With 30 participants in each group, we would have 50% power to detect an effect size of 0.52 (i.e., the sample size provides 50% sensitivity to detect a difference between groups .52 times the standard deviation of the outcome measure) and 80% power to detect an effect size of 0.74 for each of the main effects. Our primary hypothesis, however, is an interaction effect. Our sample size provides at least 50% power to detect an interaction effect size of 1.03, under this worst-case scenario. At the other extreme, if the two follow-up observations are independent, we will have 50% power to detect an interaction effect size of 0.72 and 80% power to detect an effect size of 1.03. The use of regression models further increases power by accounting for additional sources of variability. In our heart failure study, the mean difference in MSE change between Tai Chi and control was 2.26, which translates to an effect size of 1.2. Preliminary COP data from our Tai Chi for osteopenia study showed a similar effect. Therefore, we think changes of this magnitude will likely be present in the proposed study and our study has adequate power.  For Study Aim 3, we will in essence be comparing the 30 tai chi experts to the 60 novices. After adjusting for the effect of age, we will have 80% power to detect a difference between naïve and tai chi experts of approximately 0.65 times the residual error.  For Study Aim 4, we will be comparing the baseline COP and balance measures in the various age categories (15 participants age 25-35, and 20 participants in each of the older groups). This sample will provide at least 82% power to detect a difference between the young group and the average of the older groups equal to the within-group standard deviation.  ***b. Data Analysis***  *Aim 1*: We are interested in comparing the change over time in the Tai Chi students versus the controls. The primary analysis will use an intention-to-treat paradigm, i.e., participants will be evaluated on the basis of group assigned by randomization without regard to subsequent adherence. Since this is a pilot study, we will not impute values for missing data; however, the statistical models we are using will include all available data. We recognize that some participants may drop out before the follow-up evaluation and that some outcome measures may not be evaluable for some participants. We will make no adjustment for multiple testing. A secondary ‘per-protocol’ analysis will be limited to participants who were compliant (attended 70% of classes and completed at least 70% of home sessions).  Our primary analysis will employ linear mixed effects regression models that examine change over time (i.e., slope) for each outcome measure (i.e., the complexity measures, MSE and detrended fluctuation analysis) for each of the systems (i.e., heart rate, balance and gait). The models will incorporate a random intercept and a random slope for each participant. The models will be of the form:  ****  for individual  in treatment group  where the random intercept , the random slope , and the residual error . The focus of the primary analyses is on , which evaluates whether treatment is associated with the slope over time.  We will also conduct sensitivity analyses that incorporate additional covariates into the models, including age, gender, baseline physical and mental health, BMI, expectancy, and exercise behavior. We are particularly interested in examining age with a focus on assessing whether age substantially reduces the variability of the random effects, i.e., whether it explains a substantial proportion of between-person variability in baseline complexity and slope.  Analyses of secondary outcomes will follow the same general analytic approach. We will use mixed effects models to examine the effects of Tai Chi training over time on physical and cognitive function (exercise capacity, balance, upper and lower extremity strength, cognitive function, and quality of life) and adaptive capacity (change in heart rate, change in COP displacement, change in stride variability).  *Aim 2*: We hypothesize that function and adaptive capacity are associated with complexity. We will first examine the association between complexity measures and function/adaptive capacity at baseline. We will calculate Pearson correlation coefficients between the complexity measures (MSE and detrended fluctuation analysis) and the measures of function/adaptive capacity. To examine the independent association between complexity and function/adaptive capacity, we will fit ordinary least squares regression models using the function/adaptive capacity measures as the dependent variable. Independent variables will include age and sex as well as any other baseline characteristics associated with the function variable. We will add the complexity measure to this model and evaluate the Wald test and the change in R^2^.  We will also investigate whether changes in complexity are associated with changes in function/adaptive capacity. We will fit linear regression models with change in function/adaptive capacity as the dependent variable and change in complexity as the independent variable of interest. Since we will have 2 observations per participant (change at 3 months and change at 6 months), we will use generalized estimating equations methods (GEE) to account for the within-person correlation. Independent variables will include the measure of function/adaptive capacity at baseline, age, sex, treatment group and time (3 vs. 6 month).  Further, we hypothesize that complexity is the primary mediator of the association between Tai Chi and improvements in adaptive capacity. We will examine this using the approach recommended by Judd and Kenny.^193^ For example, to examine whether multi-scale entropy of balance mediates the effect of Tai Chi on center of pressure response to a dual cognitive task among the older participants, we will fit 3 regression models: regress MSE on Tai Chi use; regress COP response on Tai Chi; and regress COP response on MSE and Tai Chi use. The associations seen in these models determine the existence and strength of mediation.  Despite the implicit directionality of our hypotheses, all tests will be two-sided. We recognize that we are examining a moderate number of outcomes in this study. Since it is a pilot study and has limited power, we do not intend to adjust for multiple testing.  *Aim 3:* Our goal is to compare the complexity measures, function, and resilience to perturbations between tai chi experts and those with no tai chi training or only limited training. We expect responsiveness to decrease as a function of age among the tai chi naïve participants (i.e., both randomized groups combined). We hypothesize that tai chi experts will have a generally higher level of responsiveness, and that their responsiveness will decline with age at a slower rate than naïve or novice practitioners. To examine these questions, we will fit linear regression models to the baseline responsiveness measures for all participants:    where TC is an indicator variable for the tai chi experts.  is an estimate of the difference in responsiveness between tai chi experts at age 50,  is an estimate of the change in responsiveness per year for the novice group, and is the difference in rate of change between novices and tai chi experts.  We will fit a similar model to compare the tai chi experts to the naïve and novice groups using the 6-month data for the randomized patients and the baseline data for the tai chi experts. The group variable will be a categorical variable with 3 levels.  *Aim 4:* We will calculate sample means for each of the outcomes in each age group. We will use standard one-way analysis of variance to compare the four groups. If the overall test is significant, we will use Dunnett’s test to compare the young group to each of the older age groups. |

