### C. Subject Selection

| **Study population and recruitment procedures**  Identification of Arms 1 and 2 (Tai Chi naïve older adults)  A total of 60 healthy older adults (50-79 years old) will be recruited for our study. Recruitment will target community dwellers living within the Greater Boston area. Identification of potential study participants will include a variety of procedures that we have successfully employed in our prior studies. These include: 1) Posting study brochures and flyers in ambulatory clinics associated with BIDMC’s Department of General Medicine and Primary Care and Department of Gerontology (approximately 4,000 and 1,000 patients, respectively); 2) Direct referrals from providers in these and other clinics with whom we have a long-standing working relationship (e.g. [name] is the Chair of Gerontology and Drs. [name] and [name] are staff physicians in General Medicine); 3) Advertising in various publications including the Harvard Cooperative Program on Aging newsletter on healthy aging (disseminated 3 times a year to more than 9,500 older adults) and other local periodicals targeting older adults (e.g. *Fifty Plus Advocate, The Senior Times*), as well as on internet based resources such as Craig’s list; 4) BIDMC Syncope and Falls in the Elderly (SAFE) laboratory IRB approved database, whereby [name] provides names of potentially eligible participants who have offered to participate in SAFE lab studies; 5) Flyer placement in the communities surrounding the study’s network of Tai Chi schools (e.g., community bulletin boards, libraries).  Identification of Arm 3 (Tai Chi Expert Group)  A total of 30 healthy older adults (50-79 years old) each with over five years of tai chi practice will be recruited for our study. Recruitment will target tai chi experts living within the Greater Boston area. Potential study participants will be identified through advertisement and presentations given by PI and/or other co-investigator at Tai Chi schools.  Identification of Arm 4 (Young Comparison Group)  A total of 15 healthy young adults (25-35 years old) with no prior tai chi experience will be recruited for our study. Recruitment will target young adults living within the Greater Boston area. Potential study participants will be identified through advertisement and presentations given by PI and/or other co-investigator in the community.  5.2.2. Eligibility criteria  Arms 1 and 2: Recruitment will focus on healthy, relatively sedentary, older Tai Chi-naïve adults. Eligibility criteria will be based on screens conducted by study staff and confirmed by BIDMC GCRC nursing staff.  Arm 3 (Tai Chi Expert Group): Recruitment will focus on healthy tai chi experts with over five years of tai chi practice. Eligibility criteria will be based on screens conducted by study staff and confirmed by BIDMC GCRC nursing staff.  Arm 4 (Young Comparison Group): Recruitment will focus on healthy, relatively sedentary, young Tai Chi-naïve adults. Eligibility criteria will be based on screens conducted by study staff and confirmed by BIDMC GCRC nursing staff.  Arms 1 and 2 Inclusion criteria:  • Ages 50-79  • Living within the Greater Boston area  • Willing to adhere to 6 month Tai Chi training protocol  • Patients with a history of both solid and hematologic cancer (≥ 5 years of complete remission and who do not require chronic maintenance chemotherapy). Chronic use of hormonal agents such as aromatase inhibitors and GnRH analogs, however, are permissible with the understanding that these agents do not substantially alter the cardiovascular, autonomic, and postural control systems.  • Patients with prostate cancer (Stage I or II only)  • Patients with dermatological cancer that has been completely resected with no additional incidence.  Arm 3 (Tai Chi Expert Group) Inclusion criteria:  • Ages 50-79  • Have over five years of Tai Chi practice  • Patients with history of both solid and hematologic cancer (≥5 years of complete remission and who do not require chronic maintenance chemotherapy). Chronic use of hormonal agents such as aromatase inhibitors and GnRH analogs, however, are permissible with the understanding that these agents do not substantially alter the cardiovascular, autonomic, and postural control systems.  • Patients with prostate cancer (Stage I-II)  • Patients with dermatological cancer that has been completely resected with no additional incidence.  Arm 4 (Young Comparison Group) Inclusion criteria:  • Ages 25-35  • Living within the Greater Boston area  • Patients with a history of both solid and hematologic cancer (≥ 5 years of complete remission and who do not require chronic maintenance chemotherapy). Chronic use of hormonal agents such as aromatase inhibitors and GnRH analogs, however, are permissible with the understanding that these agents do not substantially alter the cardiovascular, autonomic, and postural control systems.  • Patients with prostate cancer (Stage I or II only)  • Patients with dermatological cancer that has been completely resected with no additional incidence.  Exclusion Criteria:  • Chronic medical conditions, including: cardiovascular disease (myocardial infarction, angina, atrial fibrillation, or presence of a pacemaker), stroke, respiratory disease requiring daily use of an inhaler, diabetes mellitus, malignancies (patients with diagnosis of active cancer < 5 years ago requiring ongoing chemotherapy or use of cytotoxic agents), neurological conditions (e.g., seizure disorder, Parkinson’s, peripheral neuropathy), or other neuromuscular or musculoskeletal (requiring chronic use of pain medication) disease  • Acute medical condition requiring hospitalization within the past 6 months  • Self-reported (current) smoking or alcohol/drug abuse  • Uncontrolled Hypertension (resting SBP > 160 or DBP > 100mm Hg)  • Abnormal heart rate (resting HR > 100 bpm; <50bpm)  • Abnormal ECG (supraventricular tachyarrhythmia, atrial fibrillation, significant ST wave abnormality, 2^nd^ and 3^rd^ degree heart block)  • Pregnancy  • Current use of prescription medications including cardio- or vaso-active drugs and medications that can affect autonomic function including Beta agonists and antagonists, drugs with anticholineric properties (e.g. tricyclic antidepressants or anti psychotics), and cholinesterase inhibitor^[[1]](#footnote-1)^  • Self-reported inability to walk continuously for 15 minutes unassisted^[[2]](#footnote-2)^  • Regular Tai Chi practice within past 5 years‡‡  • Regular participation in physical exercise on average 4 or more times per week‡‡  Arms 1 and 2 Recruitment, enrollment and randomization procedures  Potential participants who learn about our prospective study from brochures, referrals, or advertisements will be directed to call the study coordinator, who will conduct an initial eligibility screen by telephone, and schedule potentially eligible individuals for a visit at the BIDMC Clinic Research Center (CRC) for further screening. The coordinator will also discuss the randomization process and emphasize the 6 month commitment for those randomized to Tai Chi. Phone screen eligible individuals will be asked to visit at least one Tai Chi school prior to the on-site CRC screening visit. At the end of our initial phone screen, all participants will be informed about the Syncope and Falls in the Elderly (SAFE) Laboratory Research Recruitment Repository Database, and if they agree, their contact information will be given to [name]. [name] is the director of the SAFE Lab, PI of the Research Recruitment Repository Database, and a co-investigator on this study. Prior to baseline testing, individuals will undergo formal consenting following BIDMC and NIH guidelines. Following baseline testing, participants will be randomly assigned to one of two interventions, Tai Chi or wait list control.  Our study statistician, [name] will be responsible for randomization procedures. We will stratify participants by age (50-59, 60-69, 70-79), generate treatment assignments using a permuted-blocks randomization scheme with randomly-varying block sizes, and seal the treatment assignments in opaque, sequentially numbered envelopes for each stratum. The use of stratification will limit the potential for confounding by age. Upon randomization, study staff will enter the participant’s name and medical record number into a randomization log. All randomization materials will be stored in a locked file, with access limited to non-blinded study personnel.  Arm 3 (Tai Chi Expert Group) Recruitment and enrollment procedures  Potential participants who learn about our prospective study from referrals or advertisements will be directed to call the study coordinator, who will conduct an initial eligibility screen by telephone, and schedule potentially eligible individuals for a visit at the BIDMC Clinic Research Center (CRC) for further screening.  Arm 4 (Young Comparison Group) Recruitment and enrollment procedures  Potential participants who learn about our prospective study will be directed to call the study coordinator, who will conduct an initial eligibility screen by telephone, and schedule potentially eligible individuals for a visit at the BIDMC Clinic Research Center (CRC) for further screening.  Remuneration  Arms 1 and 2: All parking expenses associated with CRC visits will be paid for by the study. Eligible and consented participants who complete outcome assessments will be paid $100 at study midpoint (3 months), and $100 at study endpoint (6 months) with a maximum compensation of $200. Participants who complete the screening process but are not eligible to participate further will receive $50.Tuition for all Tai Chi training over the 6-month study period will be paid for by the study. Participants in the control group will also be offered 3 months of free Tai Chi training at the completion of the study at their choice of school within our network.    Arm 3 (Tai Chi Expert Group) Remuneration:  All parking expenses associated with CRC visits will be paid for by the study. Eligible and consented participants who complete outcome assessments will be paid $200 following single visit.  Arm 4 (Young Comparison Group) Remuneration:  All parking expenses associated with CRC visits will be paid for by the study. Eligible and consented participants who complete outcome assessments will be paid $50 following single visit. |

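### The Aim 1 slope model appears to give each arm its own baseline mean; if so, the primary test is valid but less precise than the data allow

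*Protocol*

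**What the plan says.** Under Statistical Considerations, Data Analysis, Aim 1, the protocol states: "Our primary analysis will employ linear mixed effects regression models that examine change over time (i.e., slope) for each outcome measure". Each participant has a random intercept and a random slope, and the tested term asks whether treatment is related to the slope. The model equation is not legible in the text at hand, so its fixed effects cannot be read directly.

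The same section wants to know how far age explains between-person variation in baseline complexity and in slope. Baseline is therefore a response value. The covariates named for sensitivity analyses are age, gender, physical and mental health at baseline, BMI, expectancy and exercise behaviour. The outcome's own baseline is not among them. Secondary outcomes follow the same approach.

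The sample size paragraph gives "80% power to detect an effect size of 0.74 for each of the main effects. Our primary hypothesis, however, is an interaction effect". For the interaction it says "Our sample size provides at least 50% power to detect an interaction effect size of 1.03, under this worst-case scenario", and, if the two follow-up values are independent, "we will have 50% power to detect an interaction effect size of 0.72 and 80% power to detect an effect size of 1.03". It states that no estimate of the within-participant correlation is available.

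Section C, Subject Selection, fixes the order of events: "Following baseline testing, participants will be randomly assigned to one of two interventions, Tai Chi or wait list control".

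**The concern.** Randomisation after baseline testing makes the true baseline means of the two arms equal. A model with a treatment main effect ignores this and estimates two baseline means. Chance imbalance at baseline then passes in full into the estimated slope difference, and the 3-month visit gets no weight when data are complete.

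The trial has 30 participants per arm and calls its own power limited. One stated purpose is to provide preliminary effect sizes for a larger trial. At stake is the width of the intervals around those estimates, for the primary complexity measures and for every secondary outcome analysed the same way.

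**Working it through.** **Inputs.** From the protocol: 30 per arm, visits at 0, 3 and 6 months, two-sided tests. Assumed: alpha 0.05 (not stated, but it reproduces the stated figures), SD 1 at each visit, and one within-person correlation ρ between all visits (compound symmetry) with no random-slope variance. Because the protocol gives no ρ, a range is shown. Power is from the noncentral t distribution with 58 degrees of freedom.

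**1. The plan's own figures.** A two-sample t-test with variance 2/30 gives 50.8% power at 0.52 and 80.5% at 0.74, matching "With 30 participants in each group, we would have 50% power to detect an effect size of 0.52" and "80% power to detect an effect size of 0.74 for each of the main effects". Doubling the SD gives 50.1% at 1.03 (the worst-case interaction). Multiplying it by √2 gives 49.2% at 0.72 and 79.2% at 1.03 (independent follow-ups). All agree with the protocol to within a point.

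**2. Separate baseline means.** Scale time as x = (0, 0.5, 1), so that the coefficient is the 6-month effect. With a treatment main effect, x is centred to (−0.5, 0, 0.5). The slope is then exactly month 6 minus month 0, and month 3 has weight zero. A random slope does not change this with complete data. The variance of the arm difference is

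(2/30) × 2(1−ρ).

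**3. Common baseline mean.** Without the treatment main effect, the variance is (2/30) / (x′V⁻¹x). Under compound symmetry

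x′V⁻¹x = (5+ρ) / [4(1−ρ)(1+2ρ)].

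The variance ratio, common to separate, is therefore 2(1+2ρ)/(5+ρ). At ρ = 0.5 this is 4/5.5 = 0.727, and month 3 then has weight 0.18.

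**4. Size.** Interval narrowing is 1 − √ratio. The power column takes, at each ρ, the effect at which the separate-means test has 80% power.

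| ρ | Variance ratio | Interval narrower by | Power, from 80% to | Power at effect 1.2, separate → common |
|---|---|---|---|---|
| 0.3 | 3.2/5.3 = 0.604 | 22% | 95% | 97.1% → 99.9% |
| 0.5 | 4.0/5.5 = 0.727 | 15% | 91% | 99.5% → about 100% |
| 0.7 | 4.8/5.7 = 0.842 | 8% | 86% | about 100% for both |
| 0.9 | 5.6/5.9 = 0.949 | 3% | 82% | about 100% for both |

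At ρ = 0.5 the gain is worth 30/0.727 ≈ 41 participants per arm under the separate-means model, or about 11 more per arm.

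**5. With random-slope variance.** In five settings with baseline-to-month-6 correlations from 0.38 to 0.62, the common-baseline model had 87.8% to 93.2% power where separate means had 80%.

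**6. Which model do the power figures suggest?** At ρ = 0, separate means give 50% power at 0.73 and 80% at 1.04, close to the protocol's 0.72 and 1.03. A common baseline would give about 99% power at 1.03, and its 80% detectable effect is 0.68 or less at every ρ checked from 0 to 0.9. The stated figures therefore fit separate means and do not fit a common baseline.

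**The case against.** **The equation cannot be read.** A model with time and treatment by time, and no treatment main effect, fits every legible word of the Aim 1 text, and it is the model recommended here. The sample size figures are also generic: four independent cells of 15 give 50.0% at 1.03, and four cells of 30 give 49.8% at 0.72 and 79.9% at 1.03. That is two-by-two arithmetic, not a random-slope calculation. This stands in part. The figures show that the sponsor was thinking of an interaction alongside a treatment main effect, but they do not prove what the fitted equation contains. A reader might take separate baseline means as established; they are a supported inference.

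**The size depends on choices.** A reader might infer a loss of about 10 power points. That needs ρ = 0.5 and an effect of 0.74, which the protocol gives for main effects and not for its primary interaction hypothesis. At the expected effect of 1.2 the power gain is small. This stands for power. It does not apply to interval width, which is independent of the effect size.

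**The planned test is valid.** A reader might infer bias. Nothing supports that: in a simulation of 4,000 trials, type I error was 5.1% to 5.6% for both the change-score and the baseline-adjusted comparison.

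**Aim 2 is no contradiction.** Its change models do adjust for baseline: "Independent variables will include the measure of function/adaptive capacity at baseline, age, sex, treatment group and time (3 vs. 6 month". But they relate one change to another, a different question, so Aim 1 is not inconsistent with them.

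**Zero weight for month 3 needs complete data.** The protocol expects some dropout, so this is an idealisation.

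**Conclusion.** The point holds as a question of efficiency, conditional on the equation having separate baseline means. In that case the primary comparison is an unadjusted change score when data are complete, and its interval is wider than it need be. A common baseline mean would narrow it by about 22% at ρ = 0.3, falling to 3% at ρ = 0.9, under compound symmetry with equal variances. If the equation already has a common baseline mean, the point falls away.

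The case for changing rests on precision. If the expected effect of 1.2 materialises, the planned test already has at least 97% power for ρ of 0.3 or more. That figure comes from a heart failure study, with similar preliminary balance data from the osteopenia study, whereas this trial enrols healthy adults and the protocol claims no such effect for the secondary outcomes.

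**What to change.** Confirm the fixed effects in the Aim 1 model. Unless it already does so, specify time and treatment by time with one baseline mean for both randomised arms and no treatment main effect. Keep the random intercept, the random slope and the use of all available data, and apply the same form to the secondary outcomes.

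Moving the baseline value to a covariate for the 3- and 6-month values gives nearly the same precision (variance ratio 0.75 at ρ = 0.5, using month 6 alone). It suits this protocol less well, because it takes baseline out of the response and the protocol wants to study between-person variation in baseline complexity.

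The cost is one sentence and one fewer fixed-effect term. No new data, visits or participants are needed.
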